### Nurses’ training

Intervention nurses will receive a training session from the principal investigator and a local nurse expert in motivational interviewing and geriatric care to standardise the intervention prior to the study. Firstly, nurses will receive a two-hour one-on-one training by the principal investigator. Nurses will be informed of the study objectives, procedure, detailed intervention protocol, and ethical considerations. Training sessions will involve medication self-management support, teach-back techniques, shared decision making, and basic motivational interviewing skills, e.g., posing open-ended questions, reflective listening, and expressing empathy [34]. Nurses will also receive a detailed study protocol and a manual containing instructions for delivering the intervention. Then, nurses will receive 70 min of video training on how to implement motivational interviewing techniques in the intervention. The videos are developed specifically for this program by the local nurse expert. Before the implementation of intervention, nurses’ acquisition of the above skills will be assessed by the principal investigator and the local nurse expert through a practicum with simulated patients to demonstrate their abilities to deliver the intervention.

### Outcome assessment

The researcher masked to the participant allocation will collect follow-up data through telephone interview. Participants will be assessed at T0, T1, and T2. Table 2 provides an overview of primary and secondary outcomes as well as covariates at each time point. Permission will be obtained from the original authors to use the scales for this study.

**Table 2 Tab2:** Schedule of enrolment, interventions, and assessments

TIMEPOINT	STUDY PERIOD				
	Enrolment	Baseline	Intervention	Follow-up	
		T0		T1	T2
**ENROLMENT:**					
Eligibility screen	X				
Informed consent	X				
Allocation		X			
**INTERVENTIONS:**					
Intervention group			X		
Control group			X		
**ASSESSMENTS:**					
**Primary outcome**					
Medication adherence (MARS-5)		X		X	X
**Secondary outcomes**					
Medication knowledge (PKMUQ)		X		X	X
Medication beliefs (BMQ)		X		X	X
Medication social support (MSSS)		X		X	X
Medication self-efficacy (SEAMS)		X		X	X
Medication skills (self-developed scale)		X		X	X
Medication treatment satisfaction (TSQM)		X		X	X
Treatment burden (TBQ)		X		X	X
Quality of life (EQ-5D-5L)		X		X	X
Utilisation of healthcare services (six-item questionnaire)		X			X
**Potential covariates**					
Socio-demographics (Patients questionnaire)		X			
Number of prescribed medications (one-item question)		X			
Disease burden (CIRS-G)		X			
Depressive symptoms (PHQ-9)		X			

### Primary outcome

#### Medication adherence

The Chinese version of MARS-5 will be administered to assess medication adherence of the participants [31]. The MARS-5 is a self-reporting measure of unintentional and intentional medication non-adherent behaviours with a 5-point Likert scale response ranging from 1 = always to 5 = never. The total score of the MARS-5 ranges from 5 to 25, with a higher score representing higher adherence to medication. A total score less than 20 indicates nonadherence to medications [35]. The MARS-5 has been demonstrated a reliable and valid scale for measuring medication adherence across a range of chronic conditions (Cronbach’s alpha ranged from 0.68 to 0.89) [36–38]. The internal consistency reliability of the MARS-5 among patients with multimorbidity was 0.75 [39]. The association between MARS-5 and electronic monitoring-based adherence ranged from 0.42–0.67 among patients with multimorbidity [39]. The MARS-5 has also been validated in Chinese patients with various chronic conditions with good reliability (Cronbach’s alpha = 0.762), content validity, and criterion-related validity [35, 40, 41]. The Chinese version of the MARS-5 showed satisfactory internal reliability (Cronbach’s alpha = 0.908) among older patients with multimorbidity in our previous study [27, 28].

### Secondary outcomes

#### Medication knowledge

The Patients’ Perceived Knowledge in Medication Use Questionnaire (PKMUQ) is used to determine participants’ medication knowledge [42]. The PKMUQ comprises five items covering two dimensions: general knowledge in medication use and drug interaction knowledge. The response scale ranges from 1 = strongly disagree to 5 = strongly agree, and the response scores of all 5 items will be summed. Higher scores indicate a higher level of medication knowledge. The Chinese version of the scale has well content validity and showed to be reliable for the whole scale (Cronbach’s alpha = 0.647), the general knowledge subscale (Cronbach’s alpha = 0.912), and the drug interaction knowledge subscale (Cronbach’s alpha = 0.861) [43]. The test-retest reliability coefficients over a 2- to 4-week period for the whole scale and subscales were more than 0.7 [43]. The Chinese version of the PKMUQ showed good internal reliability (Cronbach’s alpha = 0.723) among older patients with multimorbidity in our previous study [27, 28].

#### Medication beliefs

Medication beliefs will be measured by using the Beliefs about Medication Questionnaire (BMQ). The BMQ is an 18-item self-reported questionnaire consisting of two subscales: the BMQ-Specific which evaluates representations of medications prescribed for personal use and the BMQ-General which evaluates beliefs about medications in general [44]. The BMQ-Specific subscale consists of two subscales: the 5-item Specific-Necessity subscale assesses beliefs about the necessity of medications and the 5-item Specific-Concerns measures concerns about the medications. The BMQ-General contains 8 items which include two 4-item subscales: the General-Harm subscale which evaluates beliefs about the harm of medication and the General-Overuse subscale which evaluates beliefs about overuse of medication by doctors [35]. Participants will be asked to rate the degree of agreement with each statement. A 5-point Likert scale ranging from 1 = strongly disagree to 5 = strongly agree is used. A higher score indicates stronger beliefs about the corresponding concepts in each subscale. The Chinese version of BMQ with proven good reliability and validity has been widely used. The Cronbach’s alpha of overall Chinese-version questionnaire was 0.738. The factor analysis explained 55.42% of the total variance, indicating an acceptable construct validity [45]. The Chinese version of the BMQ showed acceptable internal reliability (Cronbach’s alpha = 0.639) among older patients with multimorbidity in our previous study [27, 28].

#### Medication social support

Medication social support will be assessed by the self-administered 8-item Medication-Specific Social Support Questionnaire (MSSS). Participants will be asked how often others help them with their medications over 3 months [46]. Each item is scored on a 5-point scale ranging from 0 = never to 4 = very often. A single score is derived from the mean of all items, with a higher score indicates more medication social support. A previous study has demonstrated the scale’s reliability and validity [46]. The Chinese version of the MSSS showed satisfactory internal reliability (Cronbach’s alpha = 0.878) among older patients with multimorbidity in our previous study [27, 28].

#### Medication self-efficacy

The Self-Efficacy for Appropriate Medication Use Scale (SEAMS) will be used to determine participants’ medication self-efficacy [47]. The SEAMS consists of 13 items that evaluate participants’ confidence in taking medications under various challenging circumstances. Each item has a 3-point scale ranging from 1 = not confident to 3 = very confident. The score of scale ranges from 13 to 39, with a higher medication self-efficacy by a higher score. The Chinese version of SEAMS is a reliable and well-validated measure to assess medication self-efficacy (Cronbach’s alpha = 0.915) [48]. Two factors were extracted by principal component analysis, which accounted for 60.86% of the total variance. A significant positive correlation was found between the Chinese version of SEAMS and general self-efficacy scale (*r* = 0.531, *p* < 0.001). The 10-day test-retest reliability of the scale was also acceptable (*r* = 0.642) [48]. The Chinese version of the SEAMS showed satisfactory internal reliability (Cronbach’s alpha = 0.935) among older patients with multimorbidity in our previous study [27, 28].

#### Medication skills

A medication skills assessment scale is developed for the current study and used to determine how hard or easy for patients to apply skills in medication self-management. The scale contains six items related to the skills which participants will receive in the intervention sessions. Participants respond to questions using a 5-item scale ranging from 1 = very hard to 5 = very easy. The score from each item can be summed to yield a total score and a higher score indicates a higher level of medication skills. The reliability and feasibility of the assessment scale will be tested prior to the initiation of the intervention, which will be reported elsewhere.

#### Medication treatment satisfaction

Medication treatment satisfaction will be assessed using the Treatment Satisfaction Questionnaire with Medication (TSQM) Version II [49]. The 11-item TSQM Version II scale comprises four dimensions: effectiveness, convenience, side effects, and global satisfaction. Response options are in 5- or 7- point Liker-type format. Item scores can be summed into a total score ranging from 0 to 100, with a higher score indicating higher convenience, better effectiveness, higher global satisfaction, and fewer side effects. The Cronbach’s alpha for the Chinese version of TSQM Version II was 0.707 and ranged from 0.847 to 0.961 for each subscale [43]. The test-retest reliability coefficients over a 2- to 4-week period were 0.982 for the whole scale and ranged from 0.930 to 0.995 for each subscale. Three factors were extracted by factor analysis to contribute to 73.26% of total variance [43]. The Chinese version of TSQM Version II showed good internal reliability for the total scale (Cronbach’s alpha = 0.860) and each subscale (Cronbach’s alpha ranged from 0.735–0.983) among older patients with multimorbidity in our previous study [27, 28].

#### Treatment burden

The treatment burden will be measured by the 15-item Treatment Burden Questionnaire (TBQ) [50, 51]. It assesses a broad range of behavioural and emotional burden in the procedure of undertaking and engaging treatments associated with medication-taking, self-care activities, and healthcare costs. The scale consists of three domains of treatment burden: (1) medication regimen (4-item), (2) navigating the healthcare system (5-item), (3) lifestyle changes, social and financial impacts (6-item) [52]. Each item is scored on an 11-point Likert scale, ranging from 0 = not a problem to 10 = big problem. Scores are summed to derive a total score ranging from 0 to 150 with a higher score indicating a higher level of treatment burden. The TBQ is a valid and reliable measure for patients with chronic conditions across several countries with the Cronbach’s alpha = 0.89 [50, 51]. The Chinese version of TBQ has been validated among patients with multimorbidity [53]. The Cronbach’s alpha was 0.842 and 2-week test-retest reliability was 0.830. Spearman’s correlations were over 0.4 for all items indicating adequate internal construct validity. Results of factor analysis showed a three-factor structure model with adequate goodness-of-fit. The Chinese version of TBQ showed satisfactory internal reliability (Cronbach’s alpha = 0.886) among older patients with multimorbidity in our previous study [27, 28].

#### Quality of life

Participants’ quality of life will be measured by EuroQol-5D-5L (EQ-5D-5L). It has been widely used in measuring generic health status, population health surveys, and health economic evaluations. The EQ-5D-5L consists of a five-dimension descriptive system (i.e., mobility, self-care, usual activities, pain/discomfort, and anxiety/depression) and a visual analogue scale (VAS) [54]. The five-dimension descriptive system is described at five levels (no problems, slight problems, moderate problems, severe problems, and extreme problems). The VAS is participants’ self-report health status ranging from 0 (worst imaginable health state) to 100 (best imaginable health state). A summary index score will be calculated based on the value set for the Chinese population developed by Luo et al. [55]. The EQ-5D-5L has been validated in the Chinese population (Cronbach’s alpha = 0.624). Factor analysis for construct validity showed two factors explaining 61.21% of total variance [56].

#### Utilisation of healthcare services

The utilisation of healthcare services will be assessed via a self-reported questionnaire. Information about the number of CHC visits, number of outpatient consultations, number of emergency department visits, number of hospital admissions, days in the hospital, and medical costs over the last 3 months will be collected at baseline and at 3 months after the intervention.

### Potential covariates

#### Socio-demographic characteristics and the number of prescribed medications

Socio-demographic characteristics will be collected at baseline from patients. Patients will be asked about age, gender, educational level, marital status, insurance status, monthly income, and the number of prescribed medications.

#### Disease burden

The Cumulative Illness Rating Scale-Geriatric (CIRS-G) will be used to estimate disease burden [57]. It rates the severity of diseases across 14 organ systems on a 5-Likert point that ranges from 0 = no problem to 4 = extremely severe. The total score is the sum of each of the individual system score, with a higher score representing higher disease burden. The researcher will score the severity of diseases in each system according to the guideline for scoring the CIRS-G developed by Salvi et al. [58]. The scale and the scoring guideline have both been translated into Chinese and validated among Chinese older people [59]. CIRS-G has been recommended to be used for evaluating multimorbidity in older patients by Chinese experts [60].

#### Depressive symptoms

Depressive symptoms will be measured by the Patient Health Questionnaire-9 (PHQ-9), which is the most commonly used instrument for screening depression [61]. Participants will indicate how often each statement applied to them in the last 2 weeks on a 4-point Likert scale ranging from 0 = not at all to 3 = nearly every day. Items are summed to obtain a total score ranging from 0 to 27. A score of 10 or more is used to indicate depression conditions [62]. The PHQ-9 is a validated instrument with good internal consistency among the general Chinese population (Cronbach’s alpha = 0.86). The 2-week test-retest coefficient of the Chinese-version PHQ-9 was 0.86. Construct validity was supported by one factor that accounted for 48.9 of total variance. The PHQ-9 also had good concurrent validity with the self-rating depression scale (*r* = 0.29, *p* < 0.001) and with subscales of the 36-item short form health survey (r ranged from − 0.11 to − 0.47, *p* < 0.001) [63]. The Chinese version of PHQ-9 showed good internal reliability (Cronbach’s alpha = 0.759) among older patients with multimorbidity in our previous study [27, 28].

### Randomisation, allocation concealment and blinding

Participants per CHC will be randomly allocated to either the intervention or control group. Block randomisation stratified by site with a block size of six will be used to ensure an equal number of participants in the intervention and control group in each CHC. The randomisation and group assignment will be conducted by an independent research assistant (a nurse with a master’s degree) who is not involved in study design and intervention delivery. The randomisation sequence will be generated by using the website Randomization.com (http://www.randomization.com). After completion of baseline data collection, the research assistant blinded to the allocation order will assign the treatment group using sealed opaque envelopes based on the order of recruitment and inform participants of the study group to which they have been assigned. The intervention nurse will receive names and contact details of the participants allocated in the intervention group. This study is single-blinded. Nurses and participants are not feasible to be blinded to the group allocation because of the nature of the intervention. The researcher collecting baseline and follow-up data will be kept blind to participant allocation.

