### Study setting

The trial will be conducted at three community health centres (CHCs) in Changsha, China. In urban China, CHCs serve as major primary care providers. Community general practitioners (GPs), nurses, public health physicians, pharmacists, and a few psychologists or social workers work collaboratively to provide essential public health services to community-dwelling populations including health education, medical treatment services, and chronic disease management in these CHCs [29]. All three recruited CHCs are teaching sites of the Xiangya Nursing School of Central South University and provide primary healthcare services covering a population of 40,000 to 60,000 people. The average number of patients visiting the centre per day ranges from 100 to 300 for each CHC, which provides an adequate number of participants for the trial.

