### Recruitment

At least one community nurse will be recruited from each CHC to deliver the intervention. Nurses’ inclusion criteria are (1) community registered nurse with a junior college degree or above, (2) having at least 2 years of working experience in CHCs, (3) taking on chronic disease management in routine work, and (4) not planning to quit the job in the next 6 months. Nurses who are participating in other research studies on chronic disease management at the time of this study will be excluded. Nurses will recruit participants through approaching potentially eligible participants in waiting rooms in CHCs. Centre appointments by nurses will be arranged for interested participants and the principal investigator will determine the eligibility of participants, describe the study to them, obtain written consent forms, and collect baseline data. A one-week period will be allowed for participants to decide whether or not they wish to participate in the study. Participants’ reasons for non-participation will be recorded.

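### A fixed block size of six within each centre makes some upcoming allocations deducible by unblinded nurses who appear also to recruit; the exposure is moderate and cheap to reduce before enrolment

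*Protocol article*

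**What the plan says.** All places are in the Protocol article.

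- *Randomisation, allocation concealment and blinding*: "Block randomisation stratified by site with a block size of six will be used", with the purpose "to ensure an equal number of participants in the intervention and control group in each CHC". Allocation is therefore three to three in each block, with a separate sequence per centre.
- *Study setting*: "The trial will be conducted at three community health centres (CHCs) in Changsha, China".
- *Recruitment*: "At least one community nurse will be recruited from each CHC to deliver the intervention". The same paragraph continues with the enrolment of patients: "Nurses will recruit participants through approaching potentially eligible participants in waiting rooms in CHCs". Nothing separates the nurses who recruit from those who deliver. The principal investigator decides eligibility, takes consent and collects baseline data, and patients have up to a week to decide.
- *Randomisation, allocation concealment and blinding*: "The intervention nurse will receive names and contact details of the participants allocated in the intervention group". Nurses are acknowledged to be unblinded. As a safeguard, after baseline, "the research assistant blinded to the allocation order will assign the treatment group using sealed opaque envelopes".
- *Nurses' training*: "Nurses will also receive a detailed study protocol and a manual containing instructions for delivering the intervention".
- *Intervention fidelity and contamination*: the principal investigator meets the intervention nurses and checks their logbooks every week.

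**The concern.** With a single block size, whoever counts allocations within a centre can tell when one arm of the current block is used up. From then on, every remaining place in that block is known. Opaque envelopes do not prevent this, because the inference comes from past allocations and not from the next envelope.

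A nurse who enrols patients and receives the intervention list can, in principle, infer the controls as the enrolled patients not on her list. If she then chooses whom to approach in the light of the next slot, the arms can differ in motivation or prognosis from the start. Intention-to-treat analysis and masked follow-up do not remove a difference created at entry. Adjustment for baseline variables removes only the part that those variables carry. The primary outcome is self-reported adherence, so selection on motivation would bear on it directly.

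**Working it through.** **Inputs.** Block size 6, three to three, one list per centre, three centres (*Randomisation*; *Study setting*). 136 participants, 120 evaluable, d = 0.52 (*Sample size estimation*); the plan's inflation reproduces as 120/0.88 = 136.4. The plan gives no figure for predictability.

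**1. Certain allocations, no lag.** There are C(6,3) = 20 equally likely blocks. A place is certain once three of one arm have gone. The probabilities for places 1 to 6 are 0, 0, 0, 2/20 = 0.10, 8/20 = 0.40 and 1.00. The sum is 1.5 of 6, or **25%**, half of it intervention and half control.

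**2. At this trial's size.** Incomplete last blocks lower the share. Centres of 45, 45 and 46 (an assumed even split) give 31.6/136 = **23.2%**. An assumed 30, 46 and 60 gives 33.1/136 = **24.3%**.

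**3. Best guess.** Always naming the arm with more places left, and tossing a coin when tied, is right **68.3%** of the time in complete blocks, against 50% by chance.

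**4. With a lag.** Suppose k other participants are enrolled between the approach and the assignment. The nurse then sees k fewer allocations when she chooses.

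| k | Certain places per block | Share |
|---|---|---|
| 0 | 0.10 + 0.40 + 1.00 = 1.5 | 25% |
| 1 | 0.10 + 0.40 = 0.5 | 8.3% |
| 2 | 0.10 | 1.7% |
| 3 or more | 0 | 0% |

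**5. Effect on the test.** The documents give no size for any such selection. Assume that a certain slot is filled with a patient whose expected outcome is shifted by δ = 0.2, 0.3 or 0.5 SD.

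- *Both directions, no lag.* Bias ≈ 2 × 0.232 × δ = 0.09, 0.14 and 0.23 SD, against the planned 0.52. With 60 per arm the standard error is √(2/60) = 0.183 SD. For δ = 0.2 the shift is 0.093/0.183 = 0.51, and P(Z > 1.96 − 0.51) + P(Z < −1.96 − 0.51) = 0.080. Simulation (46, 45 and 45 participants, 12% loss, unadjusted t-test) gives about **8%, 11% and 23%**.
- *Intervention slots only, no lag.* Bias ≈ 0.232 × δ = 0.05 to 0.12 SD. Type I error is about **6% to 10%**.
- *Both directions, k = 1.* Type I error is about 5.4% to 7%. With k = 2 it is about 5%.

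**6. Varied blocks, no lag.** With sizes drawn at random from 4, 6 and 8, and an observer who knows the set but not the order, simulation with 45 per centre gives a certain share of 2.2%, against 23.3% for fixed six. The best-guess rate is 67.5% in both cases. Sizes 4 and 6 alone give 5.6% certain.

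**The case against.** **Several steps separate approach from assignment.** After the approach come an appointment, eligibility and consent by the principal investigator, up to a week to decide, and baseline. Envelopes follow the order of recruitment. Some patients will fail screening, and the plan allows for 40% declining. *Trial status* plans recruitment from June to August 2020. If that means about 13 weeks and an even spread, 136/(3 × 13) ≈ 3.5 are enrolled per centre per week. A patient who uses the full week would then usually have two or more enrolments in between. This stands, and it is why 25% is only an upper bound. It does not close the route, because some patients will decide the same day and probabilistic guessing remains.

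**The nurse does not decide eligibility.** True, and a real safeguard. But the person who does meets the intervention nurses and reads their logbooks weekly, and so also has a path to past allocations.

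**Stronger readings that the text does not support.**
- A reader might infer that nurses know a quarter of upcoming allocations. That requires knowledge of the block size and of the full enrolment order, and no lag. Nurses are given intervention names only and must infer the controls, which is harder where several nurses share a centre.
- A reader might infer that the nurses' protocol copy shows the block size. *Nurses' training* does not say so; equally, nothing says that it is withheld.
- That recruiting and delivering nurses are the same people is the natural reading of *Recruitment*, but it is not stated outright.
- A reader might see a flat contradiction in giving randomisation and assignment to one research assistant who is then called blind to the order. The sentence on generating the sequence names no one, so another person may have done it. The wording is ambiguous and needs clarifying.

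**Conclusion.** The point holds as a moderate weakness of allocation concealment. The design permits deduction of up to 25% of allocations with certainty (23% to 24% at 136 participants) and a 68% best guess, for an observer with the block size, the full order and no lag. A lag of one or two enrolments cuts the certain share to 8.3% or 1.7%.

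The type I error figures depend on an assumed selection effect, on every certain slot being used, and on an unadjusted comparison. The 23% figure also needs steering in both directions at 0.5 SD. The planned adjustment for baseline variables could absorb part of any such bias. These figures describe what the design allows and do not predict conduct. The sample size is unaffected. The change is still worth making, because selection bias at entry cannot be reliably repaired afterwards and *Trial status* says that recruitment had not begun.

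**What to change.** 1. Generate the centre lists with randomly varying block sizes, for example 4, 6 and 8.
2. Withhold the sizes and their order from the recruiting nurses, including their copy of the protocol and manual, and from whoever decides eligibility.
3. Have nurses invite consecutive potentially eligible attenders, so that there is little discretion to exploit.
4. State in *Randomisation, allocation concealment and blinding* that a team member other than the assigning research assistant generates the list and seals the envelopes, so that the stated blinding to the order holds.

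**Cost.** A new list before the first participant and a few sentences of text. The largest possible imbalance within a centre rises from 3 to 4 (half of the largest block). Varied blocks remove most of the certainty but leave the best guess near 68%, so steps 2 and 3 are needed as well as step 1.
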